### Data collection and data sources

Data sources for this study will include chart review from electronic medical records, human resources data, operational data, and standardized questionnaires disseminated to the NUHS@Home Implementation Team. Collected data will be consolidated into data collection forms (DCFs) on a monthly basis (i.e., 23 data points in total) by a study team member (SL). The DCFs are available in the Supplementary Material, and the data collection strategy is summarized in Table 4.

**Table 4 T4:** Data collection strategy.

DCF	Data	Participants	Data sources
DCF 1 (operational data)	• Indicators of volume and utilization • Outcome indicators • Patient satisfaction indicators • Average occupancy rates of referring hospitals • Average number of emergency department lodgers in referring hospitals • Volume of patients in each clinical pathway • Number of home visits conducted	Operations team	Chart review Clinical operations databases Patient satisfaction team
DCF 2 (service structure and organization)	• Source of service funding • Operating and shift hours • NUHS@Home Leadership & Administrative team	Program lead	Operations data
DCF 3 (clinical operations)	• Referral parameters for active clinical pathways • New/modifications in Clinical Guidelines	Clinical service lead	Operations data Chart review
DCF 4 (service development activities)	• Publicity Broadcasts (by hospital leadership) • Publicity Broadcasts (to staff) • Publicity Broadcasts (to patients) • Engagements with external organizations • Quality and Safety Review Process • New/modifications in Policies • Technology Systems Used • Infrastructure change(s) • External Service Vendors	Operations team to draft a response but all leads to review	Operations data
DCF 5 (staffing)	• Operating and shift hours • Clinical organizational staffing • Clinical staff • Staff demographics • Staff training	Clinical, nursing, pharmacy, allied health and operations lead to fill in separately	Operations data Human resources data

DCF, data collection form.

Color coding: implementation outcome, clinical outcome, outer context, inner context.

### Qualitative methods

We will embed qualitative methods in this study through two key components. First, a document analysis of monthly implementation team meeting minutes will be conducted retrospectively. A content analysis will be carried out by one of the study team members (SL) to identify key problems and implementation activities (administrative, management, operations, or clinical) each month. Following each meeting, the lead author (SK), who also leads the implementation team, will prospectively record any important matters not captured in the minutes or the quantitative DCFs, using rapid auto-ethnography approach (23). Our team has previously applied this method in acute medical settings (24), enabling the timely capture of contextual information and real-time adjustments to the implementation process. This ensures that research remains closely aligned with the evolving NUHS@Home program.

Second, we will conduct end-of-study focus group discussions with the core implementation team after quantitative data collection concludes. These discussions will be led by trained researchers, external to both the implementation and study teams, with expertise in qualitative methods and implementation research. They will be supervised by a senior implementation scientist (NS)—a non-clinician with over 20 years of experience in health services research in hospital settings. The focus groups will explore the following thematic areas: (1) what facilitated the scale-up process and why, (2) what did not work or hindered and why, (3) explanations of the implementation outcomes elicited in the first component of the study, and (4) contextual factors that were critical in success or failure of implementation and how precisely they affected the process. If needed, two additional implementation researchers from the NUS Centre for Behavioural and Implementation Science Interventions will be trained by NS to support the data collection. Each session is expected to last approximately 90 min and include 6–8 participants. If logistical challenges prevent group discussions, semi-structured interviews will be conducted instead.

### Sample size

Based on our pilot study, which averaged 8–10 patient episodes per month with a virtual capacity of 3 beds, we anticipate approximately 1,012 patients admitted to NUHS@Home over the 23-month study period. As this is a descriptive study with no comparison group, we have not set a minimum sample size target. If a sample size becomes necessary, we will submit an amendment to the ethics borad to extend the study period.

We expect 15–25 members of the implementation team will provide data (as outlined in Table 4) and in the focus group discussions. This will include service leads from clinical, nursing, pharmacy, allied health, and operations teams within NUHS@Home.

### Data analysis

Both implementation and clinical outcomes will be described descriptively over time to contextualize the scale-up process. We will also use statistical process control (SPC) graphs to examine variation in the three defined implementation outcomes over time. To determine the association of different contextual factors with these outcomes, each contextual factor will first be categorized as either continuous (e.g., bed occupancy rates of referring hospitals) or binary/descriptive (e.g., change in funding source). For continuous variables, unadjusted and adjusted linear regression will be used to statistically assess associations between the number of contextual factors and their values and each implementation outcome to determine whether certain contextual factors are more influential than others. For binary/descriptive variables, contextual events will be annotated on the SPC graphs to assess if a clinically significant relationship exists. These analyses will be supplemented with multivariable regression to adjust for potential confounders. This approach has been previously applied in a similar ‘naturalistic’ implementation evaluation of a hospital-based scaled intervention in the UK (25).

Qualitative data from focus group discussions and meeting minutes will be analyzed using Atlas.ti software, guided by Braun and Clarke's thematic analysis approach (26). Chat logs, transcripts, and observations will be coded inductively, i.e., without any theoretical preconceptions, and themes reflecting implementation aspects will be identified and summarized. In the first stage, data will be deconstructed systematically into first-order concepts. In the second construction stage, the concepts previously developed will be reassembled into new patterns and a constant comparison technique will be carried out to compare the incidents applicable to each emerging theme. The third and final stage of analysis will include the confirmation of the conceptualization of the new phenomenon and a descriptive narrative summary will be created using second-order concepts. The analysis will seek to establish whether the emerging theme represents a barrier or a driver. Results from the different methods will be triangulated for the final data analysis.

Interim analyses will be conducted every three months, with feedback provided to the implementation team as needed.

We anticipate that some data points may be missing due to the retrospective nature of the data collection from operational and administrative datasets. If the proportion of missing data is low (<10%) and missing at random, a complete case analysis will be conducted. If missingness is substantial or not random, we will apply appropriate methods such as multiple imputation or sensitivity analyses to assess its impact on the findings.

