### Study design

This is a retrospective observational cohort study to evaluate implementation outcomes using the EPIS framework during the planned scale-up of NUHS@Home over 23 months. The primary methodology will be quantitative in approach, supported by an explanatory qualitative study with the implementation team to understand which factors are associated with the assessed implementation outcomes and how. The period of data collection will begin with the transition to phase 2 (‘develop the scalable unit’), between May 2022 to April 2024.

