### Measurements and outcomes

The primary implementation outcomes—defined as ‘the effects of deliberate and purposive actions to implement new treatments […] and are distinct from service and client (patient) outcomes’ (22)—of the scale-up process are as follows:
1.Volume: number of patient admissions to NUHS@Home and associated bed days per month2.Operational efficiency: bed occupancy rate of NUHS@Home, defined as the number of bed days occupied/virtual bed capacity * number of days that month3.Adoption: proportion of patients admitted to NUHS@Home/total patients admitted to affiliated hospital wards for established clinical pathways. Within the NUHS setting, these currently include: cellulitis, urinary tract infections, gastroenteritis, dengue fever, and exertional rhabdomyolysis, but may increase with the development of new clinical pathways.Relevant clinical outcomes will include the rate of unplanned returns to hospital, 30-day readmission rate, HaH mortality rate, and rate of patient safety incidents. At the initial set-up of the NUHS@Home service, our team developed a list of patient safety indicators by reviewing inpatient hospital reporting guidelines and adapting them for NUHS@Home. These indicators include: (1) diagnosis, treatment and procedure-related complications, (2) laboratory medicine and sample-related complications, (3) peripheral venous complication-related complications, (4) medication-related complications, (5) patient falls, (6) pressure injuries, (7) sharps injury and body fluid splash related and (8) staff and visitor incidents. These indicators will be tracked throughout the study period.

In addition, basic patient demographic data (e.g., age, gender) will also be collected to provide descriptive context for the implementation analysis.

A key tenet of implementation theory is that the scale-up process and the associated outcomes of that process (summarized above) will potentially be impacted by, or at least associated with, the context of the implementation. To better understand the impact of context, we applied the EPIS framework to define contextual influences on the outcomes described above and developed a corresponding measurement plan, summarized in Table 3.

**Table 3 T3:** Measurements of contextual influences.

Measurement (per month)	Definition
Implementation outcomes (IO)	
Volume	• Number of patient episodes • Number of bed days
Operational efficiency	• Bed days occupied • Virtual bed capacity

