Adoption	• Patients admitted to NUHS@Home per clinical pathway • Total patients admitted to affiliated hospital wards for same clinical pathway
Clinical outcomes (CO)	
Clinical outcomes	• Rate of unplanned return to hospital • 30-day readmission rate • Within HaH mortality rate • Rate of patient safety issues
Outer context (OC)	
Service environment	• Bed occupancy rates of referring hospitals • Lodger volume in emergency department of referring hospitals • Number of active clinical pathways with NUHS@Home
Funding	• Source of service funding used
Institutional leadership	• Number of leadership broadcasts (and content)
External networks	• Number of engagements with external organizations
Patient/client characteristics	• Number of patients referred for each clinical pathway • % patients accepted and rejected for each clinical pathway
Patient/client advocacy	• Number of publicity material to patients and doctors
Inner context (IC)	
Organizational characteristics	• Structural changes in the organization
Leadership	• Components of leadership team
Quality and fidelity of monitoring/support	• Processes for safety review and data tracking • New policies/guidelines/clinical standard/quality indicators • Technology systems used • Volume of home visits, during and after office hours
Organizational staffing processes	• Volume of staff on service, in total, who left • Training programs for staff in existence • Referral hours (office hours, after hours, weekends)
Individual characteristics	• % staff that are permanent or rotated • Demographics, training, experience of each staff
Infrastructure	• Structure of clinical command center, pharmacy, diagnostic, lab • # of vendors, types, issues/challenges, volume of services
Patient/Client Advocacy	• Average patient satisfaction scores • % of patients who returned to hospital due to changing their mind

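### About 14 numeric contextual measures against 23 monthly data points cannot support a ranking of influence, and the sample-size section counts patients although the regressions run on months

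*Protocol article*

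**What the plan says.** The Data collection and data sources section consolidates everything by month, giving "23 data points in total". Table 3 (Measurements and outcomes) defines outcomes and contextual factors per month, for example "Bed occupancy rates of referring hospitals".

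The Data analysis section first sorts factors into continuous and binary/descriptive. Continuous factors go into unadjusted and adjusted linear regression on each implementation outcome, "to determine whether certain contextual factors are more influential than others". Binary/descriptive factors are marked as events on the statistical process control (SPC) graphs. The section then adds: "These analyses will be supplemented with multivariable regression to adjust for potential confounders". It names no confounders. The Abstract differs, because it sends binary/descriptive factors to logistic regression.

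The Sample size section says: "As this is a descriptive study with no comparison group, we have not set a minimum sample size target". Its only quantity for the cohort is an anticipated 1,012 or so patients over 23 months. It offers to lengthen the study period if a sample size is needed. The Ethics and dissemination section says that no individual patient data will be collected.

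**The concern.** The Implementation frameworks section makes contextual influences the main focus of the research, so the regressions carry the central quantitative question. Three things that bear on that question are fixed in the article itself: the number of rows (23), the list of candidate measures (Table 3) and the aim of deciding which factors matter more. A later analysis plan can choose covariates, but it cannot supply more months.

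If a ranking is produced from so few rows, the order of the factors will depend largely on chance and on which series happen to trend together. The results are meant for policy-level stakeholders, who could take a chance ordering as advice on where to invest in scale-up. The one sample-size figure does not help them judge this, because patients are not the rows of the regressions.

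**Working it through.** **The plan's own figure.** 1,012 / 23 = 44 admissions per month. The pilot rate of 8 to 10 per month held flat gives 8 × 23 = 184 to 10 × 23 = 230. A linear ramp from 3 to 25 beds (the capacities in Table 1) at the pilot rate per bed gives (8 + 8 × 25/3)/2 × 23 = 859 to (10 + 10 × 25/3)/2 × 23 = 1,073. So 1,012 is plausible under growth, although the growth assumption is not stated. It is a count of patients, not of analysis rows.

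**Rows.** 23 monthly points. The stated window, "between May 2022 to April 2024", is 24 calendar months if both end months count. The results below barely change with 24.

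**Candidate measures in Table 3 (bullets).**
- Outer context: 3 + 1 + 1 + 1 + 2 + 1 = 9
- Inner context: 1 + 1 + 4 + 3 + 2 + 2 + 2 = 15
- Total: 24
- Plainly numeric, outer: occupancy, lodgers, active pathways, leadership broadcasts, external engagements, referrals, percentage accepted or rejected, publicity material = 8
- Plainly numeric, inner: home visits, staff volume, percentage permanent or rotated, vendors, satisfaction, percentage who changed their mind = 6
- Numeric total: 14
- With the two per-pathway items split over five pathways, home visits in 2 parts and staff volume in 3: outer 3 + 1 + 1 + 5 + 5 + 1 = 16, inner 2 + 3 + 1 + 1 + 1 + 1 = 9, total 25 columns

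The split into numeric and descriptive is a reading of Table 3; the article does not label each item.

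**Entered together.** Residual df = n − p − 1.
- 14 numeric factors: 23 − 14 − 1 = 8 (9 on 24 months; 6 if complete-case analysis leaves 21 months)
- 25 split columns: 23 − 25 − 1 = −3, not estimable
- Expected R-squared with no true association = p/(n − 1) = 14/22 = 0.64 (simulation: 0.638)

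**Tested singly.** The article states no significance level; two-sided 5% is assumed.
- Tests: 14 × 3 outcomes = 42
- Expected false positives if all nulls are true: 0.05 × 42 = 2.1
- Chance of at least one, if independent: 1 − 0.95^42 = 0.88
- If admissions and bed days are separate series: 14 × 4 = 56 tests, 2.8 expected, 0.94

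**Precision of one correlation at n = 23.**
- Smallest significant |r|: t/√(t² + 21) with t = 2.080, which is 0.41
- Power = Φ(atanh(r) × √20 − 1.96); 80% is reached at |r| ≈ 0.56, or about 0.69 at 0.05/14
- Illustration: an observed r of 0.50 has z = 0.549 ± 1.96/√20 = 0.549 ± 0.438, so a 95% interval of about 0.11 to 0.76. Most pairs of factors could not be put in order.

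**Trend.** In simulation, two unrelated random walks of 23 months were significantly correlated at 5% in 51% of pairs. A random walk is a strong form of drift, so this shows the direction of the problem and does not estimate its size here. A service planned to grow from 3 to 25 beds will, however, produce trending series.

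**The case against.** The strongest reply is that the article plans less than a reader might infer. One could read it as putting all 24 measures into one mutually adjusted model, which would need 25 parameters on 23 rows and could not be fitted. The documents do not support that reading: only continuous factors go to linear regression, binary/descriptive ones are marked on the SPC graphs, and no full model is written down. The Abstract's logistic regression and the unspecific sentence on multivariable regression leave room for more terms, but that is ambiguity and not a stated model. The 14 numeric factors can be estimated together, and the article does not say that all 14 enter at once. This part of the reply stands.

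It also stands that a covariate list, a significance level and multiplicity rules are often left to an analysis plan, so their absence from the article is not the point here. R-squared is not a planned criterion; the 0.64 only shows the degree of overfitting. Independence of tests is unlikely, since occupancy is built from bed days. That affects the 88%, but not the expected count of 2.1.

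A reader might also infer that 1,012 is offered as the sample size of the regressions. It is not. The Sample size section claims no power or precision, the 23 points are stated openly, and patient numbers do bear on how precise each monthly rate is.

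Finally, the study limits itself to associations and triangulates the regressions with SPC graphs and qualitative work. That lowers the stakes. It does not make a ranking from 23 rows reliable.

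**Conclusion.** The concern holds in this form: the article sets a ranking aim that its own rows and list of measures cannot meet. On the narrow reading (14 numeric factors, three outcomes) a joint model has 8 residual degrees of freedom, single tests yield about 2 false positives by chance, and only correlations of about 0.56 or more are reliably detected. Splitting by pathway and sub-count, or letting descriptive factors into the multivariable models, makes it worse, as do shared trends. The Sample size section calls the study descriptive and counts patients, while the Data analysis section plans statistical assessment with months as rows; the two should be aligned.

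The figures assume a two-sided 5% level, all nulls true for the false-positive counts, independence for the 88%, no autocorrelation for the power figure, and the stated reading of which items are numeric. It does not follow that the planned regressions are impossible or worthless: coefficients with honest, wide intervals remain usable as exploratory estimates. This is a should-fix.

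**What to change.** 1. In the Sample size section, state that the unit of analysis for the regressions is the month. Keep the patient count for the monthly rates, and add the precision available at that number of months. Express any extension of the study period in months.
2. In the Data analysis section, name for each outcome a small number of factors (for example 2 to 3) plus a time term for the adjusted model, chosen on EPIS grounds before the outcome data are examined.
3. Report all other factors as exploratory, with intervals and false-discovery control.
4. Drop the aim of ranking factors by influence.
5. If adoption is modelled from pathway-by-month counts (5 × 23 = 115 rows if all five pathways are active throughout), include a month-level random effect or clustering. Those rows add little independent information on factors that vary only by month.

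The cost is a change of wording and one meeting to choose the factors. The downside is that most of the Table 3 measures become exploratory.

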## Discussion

This study aims to deepen our understanding of how to effectively scale up HaH interventions, which hold significant promise in addressing critical challenges in healthcare systems. Large-scale HaH programs may reduce the demand for expanding or constructing new hospitals, curb rising healthcare costs, and shift care towards more patient-centered, home-based care models.

A key emphasis of this study is the adoption of a systematic theory-driven approach to evaluating the scale-up process, with a focus on identifying both barriers and facilitators to full-scale implementation. In doing so, the study contributes to the growing body of HaH literature, aligning with current discourse that moves beyond assessing efficacy alone and toward understanding large-scale adoption strategies.

To our knowledge, this is the first study to integrate two established implementation science frameworks—the EPIS framework and the Scale-Up framework—to analyze the scaling process of HaH interventions. This integrated approach allows for a comprehensive analysis of both the process and the contextual drivers of success or failure associated with scaling. Moreover, the study design was developed in collaboration with key implementation stakeholders from the outset, ensuring practical relevance and robust assessment of real-world conditions.

Nonetheless, there are limitations. This is an observational study treating the scale-up process as a natural experiment. As such, the evaluation is based on the service as implemented, without a control group, which restricts the ability to draw causal inferences. Consequently, the findings are limited to identifying associations rather than establishing definitive causal relationships.

Although a formal cost analysis is not included in this study, we recognize that economic viability is central to the successful scale-up and long-term sustainability of HaH services. A future follow-up economic evaluation study can be conducted to assess the cost implications and potential savings of HaH compared to conventional inpatient care, to inform healthcare financing strategies and policy decisions.

Finally, while this study protocol focuses on the evaluation of implementation and understanding contextual factors from the perspective of the implementation team, we acknowledge the importance of understanding the perspectives of referring providers. A separate qualitative study is currently underway to explore providers’ perceptions of HaH, their referral decision-making processes, and perceived barriers or facilitators to referral. Findings from that work will complement the present study and help contextualize adoption outcomes.

